### Study setting

Manica and Sofala Provinces (population: approximately 4 million; Fig. 1) were selected because of the deep relationship between investigators and the local Ministry of Health as well as the absence of existing structural interventions for MH systems improvement. The Mozambican Ministry of Health has been a leader in sub-Saharan Africa in scaling-up task-shared outpatient mental healthcare led by mid-level specialist providers called psychiatric technicians. These providers can treat all categories of mental, neurological, and substance-use disorders using both pharmacological and psychosocial evidence-based interventions. In 2014, Mozambique achieved its goal of having at least one psychiatric technician providing outpatient mental healthcare in each of the 128 districts of Mozambique [18]. However, existing evidence suggests that the quality of mental healthcare in Mozambique remains low [42] due to limited financial and human resources, few opportunities for supportive supervision, training, and re-training [18], stock-outs of essential mental health medications [43], and mental health stigma [44] among other challenges [25]. In central Mozambique, over 98% of formal health services are offered through the public sector [45], improving the potential for population-level impacts for supply-side systems interventions.

### Study outcomes

Primary SAIA-MH study outcomes will be individual-level patient functional improvement (primary), medication adherence (secondary), and retention in care (secondary) (Table 3). Patient functional improvement was selected as the primary trial outcome because it had the largest relative increase in the pilot study (aOR = 3.7, 8.9% increase, improvement from 4.2 to 13.1%) and it is the ultimate goal of MH treatment as the last step in the care cascade; therefore, improvements in upstream cascade steps and process/quality indicators should be expected to also improve functional improvement. The WHODAS 2.0 for primary outcome measurement was developed by the World Health Organization (WHO) specifically to allow cross-cultural disability measurement across settings and patient populations [46]. It has good reliability, item-response characteristics, and a robust factor structure that has been replicated across sub-Saharan Africa [46–49]. In the original WHO validation study across 19 countries (9 LMICs) the test-retest reliability had an intra-class coefficient of 0.98, the total Cronbach’s alpha (*n* = 1565 across 19 countries) was 0.98 and also 0.98 for MH patients [46, 49]. The WHODAS 2.0 has been used extensively in LMICs [46–50], shows good performance among diverse MH diagnoses [51–53], has been applied successfully in Mozambique in previous studies [50], including our pilot study, and has been extensively applied in LMICs (including Sub-Saharan Africa) to evaluate functional improvement in pragmatic MH trials [54–59]. Primary study outcomes will be sourced from a census of individual-level patient records from outpatient routine care, which will also be used to populate the MHCAT tool.

**Table 3 Tab3:** Primary study outcome definitions. All patient and facility-level outcomes refer to all patients attended in outpatient mental health services in target health facilities

Outcome	Indicator	Definition
**Patient-level clinical**	Primary: functional improvement	Patients w/ ≥ 1 follow-up w/ score ≤ 10 or ≥ 50% reduction in baseline WHODAS 2.0
	Secondary: medication adherence	Patients returning for follow-up visit not missing a dose (patient report and pill counts)
	Secondary: retention in care	Patients attending scheduled follow-up appointments; and attending those appointments on time.
**Patient-level process and quality**	Vitals recorded	Patients with height, weight, and blood pressure recorded
**Facility-level process and quality**	New patient diagnosis	# of new MH patients diagnosed
	Treatment initiation	# of new MH patients starting medication
	Total patient load	# of MH patients with ≥ 1 follow-up visits in last 3 months
**Implementation outcomes**	Acceptability	% of facility staff reporting satisfaction with SAIA-MH and various strategy components
	Adoption	% of trained facility staff engaging in ≥ 1 implementation plan in first 3 months; # of SAIA-MH cycles completed in first 6 months
	Fidelity	% of teams following 5-step SAIA-MH process
	Cost	See economic evaluation section
	Penetration	% of trained facility staff engaging in ≥ 1 implementation plan during 1-year sustainment phase
	Sustainability	# of SAIA-MH cycles completed during sustainment phase; facility staff intent-to-continue-use; clinical, process, and quality outcome trends during sustainment

### Sampling and randomization procedures

Eligible facilities are public-sector Ministry of Health clinics naïve to SAIA-MH, with ≥ 100 average annual outpatient MH consultations from 2019 to 2020 and the presence of a minimum of one psychiatric technician and one psychologist. For feasibility regarding project implementation in an area with challenges during rainy season, inclusion criteria for facilities included being within a 3-h one-way drive from Chimoio City, Manica Province, or Beira City, Sofala Province. Last, quaternary or provincial hospitals were excluded due to the complexity of mental health workflows across specialty services. Given these criteria, there were 9 eligible facilities in Manica Province and 8 eligible facilities in Sofala Province (Table 5). Eligible facilities will be allocated 1:1 to intervention or control using constrained randomization to maximally balance province, level of health facility, MH human resources, number of annual outpatient MH consultations, and baseline cascade performance. Baseline cascade performance will be facility-level achievement of patient functional improvement during the 6-month baseline period (Table 3). There will be no blinding of facility assignment at the level of providers, managers, or investigators as it is not feasible given SAIA-MH implementation procedures. The only blinding will occur at the level of the outcome assessor (statistical analyst). Randomization will be conducted in Stata 16.0 using the ccrand command for covariate-constrained randomization in cluster-randomized trials [60]. The allocation sequence will be generated by the senior author ([name]) and enrollment—including informed consent—led by technical implementation leads in Mozambique ([name] and AM).

### Data collection and management

Patient- and facility-level process and quality information (Table 3) will be abstracted into a separate CommCare [61] database by study team staff. CommCare is an android-based platform to support mobile data collection specifically in low-resource settings globally. De-identified aggregate patient and visit-level data from CommCare will be directly linked to Tableau [62] data visualization software to visualize facility-level MHCAT results in real-time. MHCAT visualizations will be shared with each facility during the scheduled supervision and implementation team meetings. Separate CommCare forms will be used to track action planning, facilitation activities, mechanisms, and costs of SAIA-MH implementation. These supervision forms will be filled out by the study team during each supervision visit. Thus, primary study outcomes, implementation outcomes, and other process measures will be sourced from: (1) CommCare patient-level data collection and supervision forms/questionnaires; and (2) qualitative CFIR interviews. Monthly data will include longitudinal documentation of changes in mechanisms of effects for all 16 facilities (Fig. 4), fidelity to the SAIA-MH model (intervention only), and barriers/facilitators to implementation. During the sustainment phase, collection, and management of the CommCare and Tableau data will transition fully to the provincial statistics offices of Sofala and Manica provinces. Research and clinical staff will be trained to identify potential adverse events and instructed to report them immediately to the senior author ([name]), implementation leads ([name] and AM) and the country director for implementation activities in Mozambique (IR). Adverse events will be reported under the schedule expected by the University of Washington ethics committee.

**Fig. 4 Fig4:**
[figure not shown]
Causal pathway model of hypothesized mechanisms of SAIA-MH effects

### Primary statistical analyses

Individual-level primary, secondary, and process/quality outcome data will be analyzed using generalized linear mixed models using random effects at the facility and individual level. Family and link functions will be determined based on outcome distributions, although *a priori* specification will utilize binomial family and logit links to evaluate the odds of progressing through the MH care cascade. Absolute and percentage changes in WHODAS 2.0 scores between patients in intervention and control facilities will also be computed. Primary analyses will compare changes from the 6-month baseline to the 2-year intensive implementation period for intervention versus control facilities. Analyses will be repeated comparing effects over the sustainability phase to both baseline and implementation phases. Patient (age, sex, HIV/TB diagnosis, suicidal ideation) and health-facility adjustment factors (patient load, staff turnover or absence, distance from district/provincial headquarters) will be considered for inclusion. Sex as a biological variable will be assessed using pre-specified interaction sub-analyses to examine differential SAIA-MH effects for females vs. males. Dose-response analyses by levels of fidelity to protocol will also be examined. We will also conduct a controlled, segmented time-series analysis [63, 64] that incorporates monthly facility-level estimates from the entire 42-month study period (segmented into 6-month pre-intervention; 24-month intervention; and 12-month sustainment periods). This secondary analysis will allow assessment of SAIA-MH on number of new diagnoses, treatment initiation, total patient load, as well all other MH cascade outcomes, addressing both serial/intra-cluster correlation, and temporal patterns in SAIA-MH effectiveness. These facility-level time-series analyses will also potentially allow exploratory examination of the effects of specific systems modifications. Modifications found to have large effects will be documented as part of identifying best practices for MH care cascade improvement. All statistical analyses will be conducted blinded to study arm (intervention vs. control).

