### Overview of study design

We will implement a 3-year cluster RCT, randomizing 16 clinics currently providing outpatient mental health care to treatment (8 clinics) and attentional placebo control (8 clinics). We will include a 6-month baseline period prior to randomization, followed by a 2-year intervention or attentional placebo control period, and an additional 1-year sustainment phase (Table 2). During the 6-month baseline phase, all clinics will receive enhanced patient registries and patient tracking tools as used in the pilot study [25]. All facilities will receive monthly in-facility mentorship on the new data tools, allowing for examination of baseline cascade performance. During these monthly visits, data from the patient registries and tracking tools will be entered into the CommCare database by study staff. Following the baseline period, clinics will be randomized to the SAIA-MH implementation strategy or attentional placebo control.

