### Primary study power assessment

In the pilot, SAIA-MH increased patient functional improvement with an adjusted odds ratio of 3.7 and an absolute increase of 8.9% (4.2% control; 13.1% intervention) [25]. The intra-cluster correlation coefficient using outpatient mental health data in the same setting is estimated at 0.26 [https://pophealthmetrics.biomedcentral.com/articles/10.1186/s12963-015-0043-3]. Selected clinics in Table 4 conducted an average of 774 outpatient MH visits per 6 months in 2019–2020. In the pilot, 40% of patients returned for follow-up within 60 days in control periods; thus, we estimate target clinics will see approximately 300 follow-up patients per 6 months. Using these assumptions, we will have ≥ 90% power to detect an increase as small as 2.2% in functional improvement (primary), 3.6% for adherence (secondary), and 4.9% for retention (secondary); (Table 5).

**Table 4 Tab4:** Facility-level characteristics

Facility	Province	Mean annual outpatient mental health visits 2019–2020	Level	Number of psychiatric technicians	Number of psychologists	Minutes to drive from Provincial Capital
Nhamatanda	Sofala	4000	Rural hospital	2	3	90
Dondo Sede	Sofala	2885	Urban health center type A	1	3	40
Macurungo	Sofala	1588	Urban health center type A	1	1	15
Mafambisse	Sofala	1306	Rural health center type 1	1	1	30
Chingussura	Sofala	981	Urban health center type A	1	2	26
Mascarenhas	Sofala	752	Urban health center type B	1	2	16
Muxúngue	Sofala	1107	Rural hospital	1	1	180
Inhamizua	Sofala	664	Urban health center type B	1	1	30
Manica	Manica	3605	District hospital	2	2	1
Gondola	Manica	1314	District hospital	2	1	20
Catandica	Manica	983	District hospital	2	2	120
Sussundenga Sede	Manica	964	Rural health center type 1	1	2	60
Macate	Manica	466	Rural health center type 2	1	1	60
Nhamaonha	Manica	284	Urban health center type B	1	1	10
Vila Nova	Manica	195	Urban health center type A	1	1	15
Vanduzi	Manica	3675	Rural health center type 1	1	1	30

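### Read as random intercepts, the primary mixed model leaves clinic-specific drift between periods out of the standard error, so the 16-clinic before-after comparison is anti-conservative to a degree the protocol's figures cannot fix

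*Protocol article*

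**What the plan says.** Under Primary statistical analyses, the article states that individual-level primary, secondary and process outcomes "will be analyzed using generalized linear mixed models using random effects at the facility and individual level". The a priori "specification will utilize binomial family and logit links to evaluate the odds of progressing through the MH care cascade". The contrast is fixed in the same section: "Primary analyses will compare changes from the 6-month baseline to the 2-year intensive implementation period for intervention versus control facilities".

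The Overview of study design describes "randomizing 16 clinics currently providing outpatient mental health care to treatment (8 clinics) and attentional placebo control (8 clinics". Under Sampling and randomization procedures, "Randomization will be conducted in Stata 16.0 using the ccrand command for covariate-constrained randomization in cluster-randomized trials".

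No facility-by-period effect, random period slope, small-sample degrees of freedom or randomization-based test is named for the primary comparison. Serial and intra-cluster correlation are mentioned only for the secondary segmented time-series analysis.

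The power section supplies the planning figures: "The intra-cluster correlation coefficient using outpatient mental health data in the same setting is estimated at 0.26"; pilot rates giving "an absolute increase of 8.9% (4.2% control; 13.1% intervention"; and "we estimate target clinics will see approximately 300 follow-up patients per 6 months".

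**The concern.** The primary effect is an arm-by-period interaction. A facility random intercept absorbs stable differences between clinics, and those subtract out of each clinic's own change. An individual random effect captures what is constant within a patient. Neither represents a shift shared by all of a clinic's patients between baseline and implementation. If such shifts exist and have no term in the model, they are treated as binomial noise and averaged away over thousands of patients, although only eight clinics per arm were randomized.

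The article itself gives reasons to expect such shifts. It mentions medication stock-outs (Study setting), staff turnover or absence (Primary statistical analyses), and maturation and external shocks (mechanisms assessment approach). In Table 4, 12 of the 16 clinics have a single psychiatric technician. The attentional control deals with influences common to all clinics, not with chance drift of individual clinics.

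At stake is the trial's main test: chance imbalance in clinic drift could be reported as a clear SAIA-MH effect.

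**Working it through.** **Inputs from the article.** 8 clinics per arm; about 300 follow-up patients per clinic per 6 months, hence 4 × 300 = 1,200 over 24 months; ICC 0.26; event rates 4.2% and 13.1%; 90% power or more claimed for a 2.2-point increase.

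**Assumptions not in the article.** Two-sided 5% level; ICC on the latent logit scale for the type I error work; one record per patient; between-period correlation ρ of a clinic's level, varied from 1 (no drift) to 0.8.

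**Step 1: the article's own power figure (4.2% to 6.4%).**
- Parallel comparison with ICC 0.26: design effect 1 + 299 × 0.26 = 78.74. Effective n per arm is 2,400 / 78.74 = 30.5. SE = √[(0.042 × 0.958 + 0.064 × 0.936) / 30.5] = 0.057, so power is 5.7%.
- The same with ICC 0 and n = 2,400 per arm: SE = 0.0065, power 92.6%.
- Difference in differences on the proportion scale, 300 patients before and 1,200 after, ICC 0.26: with ρ = 1, SE = 0.0057 and power is 97.1%; with ρ = 0.95, SE = 0.0171 and power is 25%; with ρ = 0.90, SE = 0.0236 and power is 15%.

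In these variants, 90% is reached only when clinic-level variation drops out of the contrast. That fits a standard error governed by patient counts. It does not prove it, because Table 5 is not shown.

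**Step 2: analytic type I error of the intercept-only model, 4.2% rate.**
- Latent between-clinic variance: σ² = ICC/(1 − ICC) × π²/3 = 0.26/0.74 × 3.290 = 1.156. At ICC 0.05 it is 0.173.
- Variance of one clinic's log-odds change as the model sees it: V_model = (1/300 + 1/1,200) / (0.042 × 0.958) = 0.1036.
- Variance with drift: V_true = V_model + 2σ²(1 − ρ).
- Type I error = 2[1 − Φ(1.96 × √(V_model/V_true))].

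| ρ | ICC 0.26: V_true | Type I error | ICC 0.05: V_true | Type I error |
|---|---|---|---|---|
| 1.00 | 0.1036 | 5% | 0.1036 | 5% |
| 0.95 | 0.2191 | 18% | 0.1209 | 7% |
| 0.90 | 0.3347 | 28% | 0.1382 | 9% |
| 0.80 | 0.5659 | 40% | 0.1728 | 13% |

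**Step 3: simulation under a true null.** Logit mixed model with a facility random intercept and arm-by-period term, Wald test, 400 runs per setting. Table 4 sizes were converted as annual visits ÷ 2 × 0.40 for baseline, and four times that for implementation.

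| Rate, clinic sizes | ICC 0.26: ρ = 1 | 0.95 | 0.90 | 0.80 | ICC 0.05: ρ = 0.80 |
|---|---|---|---|---|---|
| 4.2%, equal | 5% | 34% | 44% | 52% | 11% |
| 4.2%, Table 4 | 5% | 33% | 43% | 58% | 17% |
| 13.1%, equal | 8% | 39% | 55% | 64% | 23% |
| 13.1%, Table 4 | 5% | 45% | 60% | 73% | 35% |

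A separate simulation at 4.2% with Table 4 sizes gave 32%, 45% and 57% at ICC 0.26, and 8%, 14% and 17% at ICC 0.05, for ρ = 0.95, 0.90 and 0.80.

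The simulations exceed the analytic values. One reason is that the formula puts every clinic at exactly 4.2%. With a latent variance of 1.156 around that value the average rate is about 6.5%, so there are more events and V_model is smaller.

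**Step 4: comparator.** In the Step 3 tables' runs, a t-test on the 16 clinic-level log-odds changes (16 − 2 = 14 df) rejected in 3-7% of runs in every setting.

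**The case against.** The strongest reply is that the article names the levels of the random effects, not the terms. It does not say intercept-only, and a full analysis plan that is not shown could add a random period slope and a small-sample correction. That stands as a limit: a reader might infer that the plan has ruled these out, and it has not. But the article does commit to a model for the primary test, and on its ordinary reading that model omits the term that matters.

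Staff turnover is a candidate covariate, and the time-series analysis addresses correlation over time. Both are true. The first is only to be considered and leaves residual drift unmodelled; the second is secondary. Neither repairs the primary test.

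A reader might also infer that false-positive rates of 30-50% are established. The documents do not support that. They give no between-period correlation. The ICC of 0.26 is attributed to outpatient mental health data in general, not to functional improvement, and no scale is stated. With no drift there is essentially no inflation.

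Finally, a reader might conclude that the individual random effect is simply unidentifiable. That holds only with one binary record per patient. Data collection and management refers to visit-level data, and the same sentence on random effects covers adherence and retention, which can repeat. The simulations omitted this term, so they represent the stated model only under the one-record assumption.

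**Conclusion.** The point holds on the ordinary reading of the text. With facility and individual random intercepts only, the arm-by-period standard error reflects patient numbers and ignores clinic drift, so the test is anti-conservative whenever clinics drift.

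The size is conditional. It is about 5% without drift. For assumed between-period correlations of 0.95 to 0.8 it is roughly 8-35% at ICC 0.05, the upper end coming from the 13.1% rate with Table 4 clinic sizes (the analytic value at the low end is 7%). It is roughly 18-58% at ICC 0.26 on the latent scale and a 4.2% rate, taking the analytic and simulated results together. The direction is firm; no single figure within these ranges is.

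**What to change.** Add a facility-by-period random effect, or a random period slope by facility, to the primary model, and test arm-by-period with small-sample degrees of freedom (about 14). Alternatively, make the primary test a permutation test on the 16 clinic-level changes over the constrained allocation set, and use the mixed model for estimation.

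State the analysis record for each outcome. Keep the individual-level random effect only where a patient contributes more than one record. Redo the power calculation under the same structure, over a stated range of between-period correlations.

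The cost is a change of wording in the protocol and analysis plan and a few lines of code; clinics, data collection and care are unaffected. Confidence intervals will be wider, and correct, and the detectable effect may prove larger than the 2.2 points now stated.

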### Primary study power assessment

In the pilot, SAIA-MH increased patient functional improvement with an adjusted odds ratio of 3.7 and an absolute increase of 8.9% (4.2% control; 13.1% intervention) [25]. The intra-cluster correlation coefficient using outpatient mental health data in the same setting is estimated at 0.26 [https://pophealthmetrics.biomedcentral.com/articles/10.1186/s12963-015-0043-3]. Selected clinics in Table 4 conducted an average of 774 outpatient MH visits per 6 months in 2019–2020. In the pilot, 40% of patients returned for follow-up within 60 days in control periods; thus, we estimate target clinics will see approximately 300 follow-up patients per 6 months. Using these assumptions, we will have ≥ 90% power to detect an increase as small as 2.2% in functional improvement (primary), 3.6% for adherence (secondary), and 4.9% for retention (secondary); (Table 5).

**Table 4 Tab4:** Facility-level characteristics

Facility	Province	Mean annual outpatient mental health visits 2019–2020	Level	Number of psychiatric technicians	Number of psychologists	Minutes to drive from Provincial Capital
Nhamatanda	Sofala	4000	Rural hospital	2	3	90
Dondo Sede	Sofala	2885	Urban health center type A	1	3	40
Macurungo	Sofala	1588	Urban health center type A	1	1	15
Mafambisse	Sofala	1306	Rural health center type 1	1	1	30
Chingussura	Sofala	981	Urban health center type A	1	2	26
Mascarenhas	Sofala	752	Urban health center type B	1	2	16
Muxúngue	Sofala	1107	Rural hospital	1	1	180
Inhamizua	Sofala	664	Urban health center type B	1	1	30
Manica	Manica	3605	District hospital	2	2	1
Gondola	Manica	1314	District hospital	2	1	20
Catandica	Manica	983	District hospital	2	2	120
Sussundenga Sede	Manica	964	Rural health center type 1	1	2	60
Macate	Manica	466	Rural health center type 2	1	1	60
Nhamaonha	Manica	284	Urban health center type B	1	1	10
Vila Nova	Manica	195	Urban health center type A	1	1	15
Vanduzi	Manica	3675	Rural health center type 1	1	1	30

